### Blinding

It will not be possible to blind participants or interventionists to their group assignment. It is unlikely that the lack of blinding will influence the primary and secondary physiological outcomes but it could potentially influence the patient-reported outcomes. Study staff that are blinded to group assignment and prior test results will perform CPETs and circulating biomarker analyses. All MRI analyses (i.e. the quantification of data from the images) where user input can impact data (e.g., LV volume tracing) will be blinded to group assignment and time point using random numbers.

### Sample size determination

There is no available data on the effect of short-term caloric restriction or exercise on LVEF reserve. In the pilot study of the exercise intervention there was a large effect size (Cohen’s f = 0.454) on NT-proBNP. Based on this and the sensitivity of using both MRI and exercise to elucidate subclinical dysfunction, we expect at least a medium effect size for the primary outcome in the current study (Cohen’s f = 0.25). Using *n* = 15 sample size per group for a three-arm, three-repeated measures design, there is > 90% power to detect a medium effect size at *p* = 0.05 (G*Power Version 3.0.10). This sample size is further substantiated by the finding that a 3 percentage point change in resting LVEF can be detected with cardiac MRI with n = 15 patients, an 85% reduction in the sample size required to detect the same change using echocardiography [60]. The primary outcome in the current study, LVEF reserve is expected to be more sensitive than resting LVEF and therefore this sample size is expected to detect a difference between the intervention groups and the control group. A total of *n* = 56 patients (*n* = 18–19 per group) will be enrolled to allow for a 20% rate for dropout, death, and technical difficulties.

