### Outcome measures

The study outcome measures and their timing are summarized in Table 2. The primary outcome measure is cardiac function reserve capacity (LVEF reserve), which is calculated as peak exercise LVEF – resting LVEF, at the end of anthracycline treatment relative to the control group. Despite being the primary parameter used to diagnose cardiotoxicity, it is recognized that resting LVEF is insensitive to subclinical anthracycline-related cardiac damage due to the heart’s capacity to compensate for dysfunction at rest. By the time a decrease in resting LVEF is realized, there is likely already substantial and irreversible damage to the myocardium [3]. In women previously treated for breast cancer, a systematic review demonstrated that the application of either exercise or pharmacological stress during cardiac imaging techniques identified cases of cardiac dysfunction that were not identified using resting imaging [41]. More specifically, in women receiving anthracycline treatment for breast cancer, LVEF reserve (peak – rest) and peak LVEF after two treatments were significant predictors of a resting LVEF drop to < 50% at 18 months after treatment [42].

**Table 2 Tab2:** Summary of study outcome measures

Measure	Assessment Method	72+ h pre-anth	24 h post 1st & last anth	2–3 w post last anth	1 y post 1st anth	5 y post 1st anth
Primary Outcome:						
LVEF reserve (peak – rest)	MRI	x		x	x	
Secondary Cardiac Outcomes:						
Peak and resting LVEF	MRI	x		x	x	
Resting and peak LV strain	MRI	x		x	x	
LV volumes and cardiac output	MRI	x		x	x	
Myocardial T1	MRI	x		x	x	
LV mass	MRI	x		x	x	
NT-proBNP	Venipuncture	x	x	x		
Secondary Vascular Outcome:						
Ascending and descending aortic distensibility	MRI	x		x	x	
Secondary Skeletal Muscle Outcomes:						
Lower leg oxygen extraction	MRI	x		x	x	
Lower leg oxygen consumption	MRI	x		x	x	
Thigh muscle mass	MRI	x		x	x	
Thigh muscle quality	MRI	x		x	x	
Secondary Integrative Outcomes:						
Whole body oxygen consumption reserve	CPET	x		x	x	
Treatment symptoms	Rotterdam Symptom Checklist	x		x	x	
Exploratory Outcomes:						
Tumor size	Ultrasound	x		x^a^		
Quality of life	FACT-General questionnaire	x		x	x	
Fatigue	FACT-Fatigue questionnaire	x		x	x	
Markers of oxidative stress/antioxidants	Venipuncture	x		x		
Clinical Outcomes					x	x
Safety Outcomes:						
Clinically reported symptoms	ESAS	Will be extracted from clinical records for intervention period				

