### Statistical analyses

Given the longitudinal study design, a linear mixed model analysis that includes both fixed and random effects will be used. The repeated measures on a single subject result in correlated outcome data, and the random effects allow this correlation to be explicitly modeled. An additional advantage of this model is that it allows for missing data on a subject without deleting all the data for that subject; as such imputation for missing data will not be performed. The model also allows for covariates to be tested and can include time varying covariates (e.g. treatments received post anthracyclines). One assumption of mixed models is that the residuals from the model are normally distributed. If that is not the case, a Generalized Linear Mixed model that can fit other distributions will be used. All analyses will be performed using both intention-to-treat and per protocol approaches. Although it is hypothesized is that each intervention will be effective relative to usual care, there is not a strong rationale to expect a difference in efficacy between the two interventions. However, each group will be compared against the remaining two groups to determine whether one lifestyle intervention is more efficacious or whether patient preference and tolerance can determine choice of intervention.

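### The power above 90% fits a three-time-point interaction test, not the primary comparison of each intervention with control at end of treatment, where a medium difference has far less power

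*Protocol article*

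**What the plan says.** **Sample size determination** sets the assumption: "we expect at least a medium effect size for the primary outcome in the current study (Cohen’s f = 0.25". It gives 15 per group after dropout and 56 enrolled, and claims "three-arm, three-repeated measures design, there is > 90% power to detect a medium effect size", citing G*Power at 0.05. Neither the F test nor the correlation between repeated measures is named. The section then argues that "LVEF reserve is expected to be more sensitive than resting LVEF and therefore this sample size is expected to detect a difference" between intervention and control.

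**Outcome measures** defines the primary outcome as LVEF reserve "at the end of anthracycline treatment relative to the control group". The one-year scan is described there as a check on longer-term effects.

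**Statistical analyses** specifies a linear mixed model. The hypothesis is that "each intervention will be effective relative to usual care", and "each group will be compared against the remaining two groups". Covariates may be tested in the model, but adjustment for baseline is not stated.

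**Discussion** warns that power may be inadequate, but only for the secondary outcomes.

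**The concern.** The power statement describes a design with three arms and three measurements, while the primary question concerns one measurement time and two pairwise contrasts. Cohen's f for an interaction is not on the same scale as f among group means at one time, so the word medium can stand for very different true differences. If the printed figure does not belong to the primary contrast, the protocol gives readers no usable statement of what 15 per group can detect. A non-significant primary result could then be given more weight as evidence against cardioprotection than the design allows.

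**Working it through.** **Inputs from the protocol:** k = 3 groups, 15 per group (N = 45), m = 3 measures, f = 0.25, alpha 0.05. **Assumed:** the correlation ρ (not given; range shown), sphericity, equal SDs, two-sided pairwise tests with no multiplicity adjustment.

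**1. Reproducing the stated figure.** Group-by-time interaction: λ = f²·N·m/(1−ρ), with (k−1)(m−1) = 4 and (N−k)(m−1) = 84 df.
- ρ = 0.5: λ = 0.0625 × 45 × 3 / 0.5 = 16.875, power 91.1%.
- ρ = 0.3: 78%. ρ = 0: 60%.
- Baseline and end of treatment only (m = 2), ρ = 0.5: λ = 11.25, df 2 and 42, power 83%.

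Alternatives: the between-groups main effect, λ = f²·N·m/(1+(m−1)ρ), gives 41% at ρ = 0.5 and at most 71% (at ρ = 0), so it cannot be the source. The time main effect gives 96% at ρ = 0.5 but does not compare arms.

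**2. What interaction f = 0.25 means.** Let control differ by δ (in SD) from two equally effective interventions after baseline, at one or both later times. The interaction effects are the product of the centred arm pattern and the centred time pattern, each with root mean square √(2/9). So f = (2/9)δ, and f = 0.25 gives δ = 0.25 × 9/2 = 1.125 SD.

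**3. What f = 0.25 means at the primary time.** Among three means at one time, f = √(2/9)·δ, so δ = 0.25/0.471 = 0.53 SD. A true 0.53 SD gives an interaction f of only (2/9) × 0.53 = 0.118, and about 29% power in the interaction test itself at ρ = 0.5.

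**4. Power at the primary time, 15 per group, δ = 0.53 SD.** Three-group F test at one time: λ = 0.0625 × 45 = 2.81, df 2 and 42, power 28.5%. Pairwise contrast: noncentrality = (δ/s)·√(15/2), where s = 1 unadjusted and s = √(1−ρ²) baseline-adjusted (41 df).

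| Contrast with control | Power |
|---|---|
| Unadjusted | 29% |
| Baseline-adjusted, ρ = 0.3 | 32% |
| Baseline-adjusted, ρ = 0.5 | 37% |
| Baseline-adjusted, ρ = 0.7 | 51% |
| Baseline-adjusted, ρ = 0.8 | 66% |

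For change from baseline, s = √(2(1−ρ)). At ρ = 0.5 this is 1, so power is again 29%.

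**5. Other settings.** If all 56 complete (18.67 per group): 35% unadjusted, 45% adjusted at ρ = 0.5, about 75% at 0.8. If the arms are evenly graded, f = 0.25 makes the largest pairwise gap 0.61 SD. With 15 per group that gap has 37% unadjusted, 47% adjusted at ρ = 0.5 and 78% at 0.8.

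Working backwards, 90% power with 15 per group needs about 1.21 SD on the analysed scale. For 0.53 SD, √(1−ρ²) would have to be 0.53/1.21 = 0.438, so ρ would have to be about 0.90.

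**6. Detectable difference at 80% power, 15 per group.** Unadjusted: 1.05 SD. Change from baseline at ρ = 0.5: about the same. Baseline-adjusted at ρ = 0.5: 1.05 × √0.75 = 0.91 SD.

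**The case against.** - **The number is correct for a test that fits the design.** Table 2 lists LVEF reserve at three times and the analysis is longitudinal, so a three-measure calculation is not foreign to the plan. This stands. A reader might infer that the authors made a calculation error; they did not. The fault is a mismatch between test and primary comparison. Using the one-year scan is also the minor part of it (91% against 83% at ρ = 0.5). The omnibus form and the meaning of f carry the weight.
- **The interaction test is an inference.** True, because the protocol does not name it. It is the only between-group option found that gives the figure.
- **The protocol expects at least a medium effect.** If the pilot value f = 0.454 applied at the primary time, pairwise power would be about 72% unadjusted and 84% adjusted at ρ = 0.5. But that value concerns NT-proBNP, and the printed claim is about a medium effect.
- **Power is higher for finding either intervention effective.** With both interventions at 0.53 SD and no multiplicity adjustment, the chance that at least one contrast is significant is about 43% unadjusted and 53% adjusted at ρ = 0.5. The lower figures above are per contrast.
- **Resting LVEF.** A reader might infer that reserve, being a difference of two measurements, must be noisier and so have less power than resting LVEF. The protocol does not support that either. It gives no variance for reserve and no power or design for the cited n = 15 result, subtraction removes shared between-person variation, and the signal under stress may be larger. All that follows is that resting-LVEF sensitivity is not evidence of power for reserve.

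**Conclusion.** The concern holds as a mismatch. The claim of more than 90% power for a medium effect does not apply to the primary comparison defined under Outcome measures and Statistical analyses. For f = 0.25 at end of treatment, power per contrast is about 29% unadjusted and 32% to 66% with baseline adjustment at correlations of 0.3 to 0.8. No setting examined reaches 90%; with 15 per group, two equally effective interventions and baseline adjustment, that would take a correlation near 0.9. These figures rest on the reading of medium as f = 0.25 among the three arms and on a correlation that the protocol does not give, so no single power value should be quoted as the truth.

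A reader might also conclude that the sample size must be increased. The documents do not establish this: the trial is phase II, and no target difference in LVEF points is stated against which 56 could be judged too few. What is wrong is the printed assurance, and the Discussion does not temper it for the primary outcome.

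**What to change.** Keep n = 56. In Sample size determination, remove the claim of more than 90% power for a medium effect. Replace it with power, or the detectable difference, for each intervention against control at end of anthracycline treatment. Calculate it under the model actually planned and give the assumed correlation with a range. Two forms are possible for 15 per group, two-sided 0.05 and 80% power:

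- If baseline is not adjusted for, or change from baseline is analysed at correlation 0.5: about 1.05 SD.
- If the model adjusts for baseline at correlation 0.5: about 0.9 SD. Use this form only if baseline adjustment is written into the analysis.

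Do not offer the resting-LVEF argument as evidence of power. In the Discussion, extend the caveat on power to the primary outcome.

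The cost is protocol wording. Recruitment and conduct do not change, nor does the analysis unless baseline adjustment is newly adopted. The stated power becomes less favourable.

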### Statistical analyses

Given the longitudinal study design, a linear mixed model analysis that includes both fixed and random effects will be used. The repeated measures on a single subject result in correlated outcome data, and the random effects allow this correlation to be explicitly modeled. An additional advantage of this model is that it allows for missing data on a subject without deleting all the data for that subject; as such imputation for missing data will not be performed. The model also allows for covariates to be tested and can include time varying covariates (e.g. treatments received post anthracyclines). One assumption of mixed models is that the residuals from the model are normally distributed. If that is not the case, a Generalized Linear Mixed model that can fit other distributions will be used. All analyses will be performed using both intention-to-treat and per protocol approaches. Although it is hypothesized is that each intervention will be effective relative to usual care, there is not a strong rationale to expect a difference in efficacy between the two interventions. However, each group will be compared against the remaining two groups to determine whether one lifestyle intervention is more efficacious or whether patient preference and tolerance can determine choice of intervention.

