### Randomization

Randomization will consist of a permutated block design with random block sizes of six and nine and stratification by two factors with a 1:1:1 allocation ratio. The stratification factors will include: 1) receipt of trastuzumab (yes/no), as it is also known to affect cardiac function; and 2) adjuvant/neoadjuvant protocol to ensure an equal distribution of neoadjuvant patients to assess the exploratory tumor size outcome. An external party to the study will generate the randomization sequence using a spreadsheet random function. This same individual will put the group assignment into sequentially numbered, sealed, opaque envelopes. Randomization will occur following completion of baseline assessments.

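### The exercise-versus-diet comparison is framed as an either/or with no inconclusive outcome, so failing to show a better intervention becomes grounds for treating the two as similar in a trial sized against usual care

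*Protocol article*

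**What the plan says.** The Statistical analyses section hypothesizes that each intervention will be effective relative to usual care, and adds that "there is not a strong rationale to expect a difference in efficacy between the two interventions". It then says that each group will nevertheless be compared with the other two, and gives the purpose: "to determine whether one lifestyle intervention is more efficacious or whether patient preference and tolerance can determine choice of intervention".

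The Sample size determination section rests on a medium effect (Cohen's f = 0.25) with 15 per group as the "sample size per group for a three-arm, three-repeated measures design", and reports that "there is > 90% power to detect a medium effect size at" the 0.05 level. It closes the argument by saying that "this sample size is expected to detect a difference between the intervention groups and the control group". Enrolment is 56, or 18–19 per group, "to allow for a 20% rate for dropout, death, and technical difficulties". The Outcome measures section defines the primary outcome relative to the control group at the end of anthracycline treatment. The Discussion concedes limited power for some secondary outcomes but says nothing about the contrast between the two interventions.

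**The concern.** The purpose clause has two branches: one intervention is more efficacious, or preference and tolerance can settle the choice. The second branch is reasonable only if the two work about equally well. As written, the reader reaches it whenever the first branch is not established. Failing to reject a hypothesis of no difference is then used as evidence of similarity.

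The authors see no strong reason to expect a difference, so the second branch is the one that they are most likely to reach. If the contrast is imprecise, the report could present the choice as a matter of preference while the data remain compatible with a difference that patients and clinicians would care about.

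**Working it through.** **Inputs from the protocol article.** Three arms allocated 1:1:1; 15 evaluable per group; 56 enrolled; f = 0.25; level 0.05; three repeated measures; primary visit at end of anthracycline treatment.

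**Assumptions, not in the article.** Correlation ρ between baseline and end-of-treatment values, taken from 0 to 0.8; a two-sided pairwise test; equal variances. The range of n runs from 15 per arm to 18.5, the midpoint of the stated 18–19 with no losses.

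**Step 1: the plan's own figure.** For the group-by-time interaction in a repeated-measures ANOVA, λ = f²·N·m/(1 − ρ) = 0.0625 × 45 × 3/(1 − 0.5) = 16.875, with 4 and 84 degrees of freedom. Power is 0.911, so the stated figure of more than 90% reproduces if ρ = 0.5. On dropout, 45/0.8 = 56.25, in line with 56. This is power for an overall three-arm test, not for one pair of arms.

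**Step 2: exercise versus diet at the primary visit.** For two equal groups at one visit d = 2f, so f = 0.25 corresponds to d = 0.5. The noncentrality is d/[√(1 − ρ²)·√(2/n)], with error degrees of freedom pooled over three arms (42 unadjusted and 41 baseline-adjusted at n = 15).

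- Unadjusted, n = 15: 0.5/√(2/15) = 1.369; critical t 2.018; power 0.267; miss rate 73%.
- Baseline-adjusted, ρ = 0.5, n = 15: 1.369/√0.75 = 1.581; critical t 2.020; power 0.339; miss rate 66%.

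**Step 3: interval width.** Half-width = t·√(2/n)·√(1 − ρ²). Unadjusted at n = 15: 2.018 × 0.365 = 0.74 SD. At ρ = 0.5: 2.020 × 0.365 × 0.866 = 0.64 SD.

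**Step 4: range** (true difference 0.5 SD; ρ = 0 is the unadjusted case).

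| ρ | Miss, n = 15 | Half-width (SD) | Miss, n = 18.5 | Half-width (SD) |
|---|---|---|---|---|
| 0 | 73% | 0.74 | 68% | 0.66 |
| 0.3 | 71% | 0.70 | 65% | 0.63 |
| 0.5 | 66% | 0.64 | 59% | 0.57 |
| 0.7 | 53% | 0.53 | 45% | 0.47 |
| 0.8 | 39% | 0.44 | 30% | 0.40 |

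The best case in the table has 70% power. A mixed-model contrast of changes from baseline, rather than baseline adjustment, does worse at low correlation: at ρ = 0.3 and n = 15 its power is 0.208, a miss rate of 79%.

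**Step 5: a larger difference.** For 0.8 SD at n = 15, power is 0.572 unadjusted and 0.695 at ρ = 0.5, so the miss rates are 43% and about 30%.

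**Step 6: what a non-significant result leaves open.** Non-significance means that the estimate lies within one half-width of zero, so one end of the interval lies at least one half-width away from zero. With half-widths of 0.53 SD or more, no non-significant result can exclude a 0.5 SD difference in both directions. With the narrowest ones (0.40 to 0.47 SD), an estimate close to zero could.

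**The case against.** The strongest reply is that the clause states a research question, not a decision rule. It contains no significance criterion, does not claim equivalence, and does not call the interventions interchangeable. A reader might infer that the plan commits itself to declaring equivalence from a non-significant test; the text does not go that far. What stands is narrower: the wording offers two outcomes and no third, and so permits and invites that inference.

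Second, a margin or interval criterion may sit in a full protocol or analysis plan that is not shown. That is fair, and its absence from the article is not the point. The point is the inference that the article does state.

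Third, a reader might infer that two ineffective interventions would also be handed over to patient preference. The documents do not support this well: the same sentence compares each intervention with usual care, and the sentence as a whole opens from the hypothesis that each works against it. The condition is implied, though not stated.

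Fourth, a reader might take about 70% as the miss rate, or say that the plan errs most of the time when the interventions differ. Without an SD or a correlation neither can be said so firmly: the table falls to 30%, and at 0.8 SD the miss rates are below half.

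In the plan's favour, f = 0.25 read as a two-arm by three-visit interaction at ρ = 0.5 gives 84% power with 15 per arm. With equal arms at baseline and the same gap at both later visits, however, that f means a gap of 0.25/(0.5 × √(2/9)) = 1.06 SD, which is not a medium difference between arms.

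Finally, this is an ancillary contrast in a phase II trial. That limits the stakes, but the sentence concerns how an intervention would be chosen.

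**Conclusion.** The concern holds as a fault in the stated inference. Lack of demonstrated superiority of exercise over diet, or the reverse, does not show that they are similar, and this is so at any correlation. The size of the problem depends on assumptions: a 0.5 SD difference at end of treatment, a two-sided 0.05 test, and the ranges of correlation and sample size in the table. Under these the trial misses the difference between about 30% and 73% of the time, and at no point reaches 80% power for it. The stated power of more than 90% belongs to the overall three-arm test and does not carry over to this pair. Neither the primary comparison with usual care nor any data collection is called into question.

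**What to change.** Replace the purpose clause with wording such as: *Exercise and caloric restriction will be compared by estimate and 95% CI; a difference that is not significant will be reported as inconclusive and not as evidence of similar efficacy.* Add that any statement on patient preference will quote this interval and will be made only if each intervention has been shown better than usual care.

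The cost is one or two sentences, with no extra patients, visits or data. The trial gives up a conclusion that its size cannot support.
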